### Possible outcomes

It is expected that the study will provide baseline data on children’s exposure and general household exposure to mining dust lead. The study will also reveal the effectiveness (or not) of an educational and domestic hygiene intervention in reducing childhood lead levels in a settlement located close to a mine dump. Should the study reveal a significant, positive effect, it will demonstrate the potential for a simple domestic and environmental intervention to protect communities living close to mine dumps (and potentially other sources of pollution) from exposure to associated toxic substances, specifically lead.

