**Discussion:**

The study will determine whether the intervention led to a reduction in indoor dust lead levels, and if shown to be effective, will inform the development of an awareness campaign to reduce lead exposure in communities located in close proximity to mine dumps.

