### Data collection procedure

Data will be collected using multiple methods, namely, 1) a structured questionnaire; 2) hand dust wipe samples from children aged between one and five years; 3) floor and/or windowsill dust wipe samples; and 4) yard soil samples. These methods will be applied in two phases. In phase one, participants will be allocated into either the control or intervention group (see Fig. 1). Both the control and intervention groups will be interviewed, household floor and/or windowsill dust wipes will be taken, yard soil samples collected, and hand dust wipe samples taken from children in participating households. The intervention group will participate in the domestic hygiene demonstration and educational discussion. The intervention group will be allowed a period of three months to apply the domestic hygiene intervention. Each household will be given a diary to record their daily cleaning patterns. During the three months, a monthly reinforcement visit will be undertaken to follow-up and encourage the sustained application of the intervention. In phase two, after three months, both the intervention and control group will be visited to collect a repeat floor and/or windowsill dust sample, yard soil sample and hand dust wipe sample from children. Feedback will be obtained from the intervention group on the experience of the intervention using a checklist.

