### The intervention

#### Personal hygiene intervention

At the end of the questionnaire-based interview, blood collection and environmental sample collection, participants (parents/guardians) will be engaged in an educational discussion for approximately 30 min, with the aid of a specially designed educational pamphlet (Fig. 2). The pamphlet contains information about health effects potentially associated with dust exposure from mine dumps and the personal hygiene and domestic hygiene steps that may be followed to reduce dust exposure. The pamphlet will be pre-tested during the pilot study and refined as necessary.

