## Discussion

A research study has shown that there has been significant growth in the number of households and housing developments, close to the TSFs in South Africa [15]. Furthermore, the study stated that the implications for many residences downwind mine dumps justify ongoing monitoring efforts and educational programmes [14]. Occasionally, two strategies are implemented to reduce pollution from such mine dumps i.e., spraying of mine tailings dumps with water and rehabilitation through planting grass. However, these strategies are often deemed ineffective, since grass withers during the dry season in particular, and sprayed water is rapidly absorbed or evaporated. The current extent of environmental contamination from mine dumps and potential health impacts in nearby areas has been researched, the findings showed that participants identified mine dumps as the biggest source of dust [16]. Other studies have explored the acceptability and feasibility of changing housekeeping behaviour to reduce childhood lead exposure [17]. A study by Feit et al. found that certain personal and domestic hygiene interventions were feasible and acceptable to the study community and were significantly associated with a reduction in indoor dust lead concentrations [16]. However, there is a need to conduct further trials in developing countries to determine the effectiveness of interventions for the prevention of lead [18]. A review by Nussbaumer-Streit et al. found that educational interventions were not effective in reducing blood lead levels and dust control interventions may lead to little or no difference in blood lead levels [19]. However, the quality of evidence was moderate to low, meaning that future research is likely to change these results. No further research has yet been undertaken to evaluate the impact on childhood lead levels of a community-based lead exposure reduction programme focused on personal and domestic hygiene. In particular, there remains a gap in knowledge regarding household hygiene interventions to reduce exposure to lead in communities living close to mine dumps in South Africa, particularly among children. This study, which intends to evaluate the impact of a household hygiene intervention comprised of an educational and domestic household hygiene intervention to reduce mining-related dust exposure, will address this need. The study holds the potential for a cost-effective measure to reduce exposure to mining-associated toxic substances, for hundreds of thousands of households living in the shadow of mining operations and other sites of elevated exposure to toxic substances from industrial sources.

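### The study is said to show whether the intervention lowers lead levels in children, but the measures it repeats are lead on hands, indoor surfaces and soil, which show exposure and not absorbed lead

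*Protocol article*

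**What the plan says.** Possible outcomes gives the conclusion that the study is meant to deliver: "The study will also reveal the effectiveness (or not) of an educational and domestic hygiene intervention in reducing childhood lead levels". The main Discussion echoes it by naming the effect on lead levels in childhood as the gap in knowledge, directly after a paragraph on blood lead.

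Data collection procedure lists four methods. The first is a questionnaire, and the rest are "2) hand dust wipe samples from children aged between one and five years; 3) floor and/or windowsill dust wipe samples; and 4) yard soil samples". At three months the team returns "to collect a repeat floor and/or windowsill dust sample, yard soil sample and hand dust wipe sample from children". The laboratory sections cover those three sample types only.

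Blood sampling in this study is mentioned once, under Personal hygiene intervention, where the educational session is timed: "At the end of the questionnaire-based interview, blood collection and environmental sample collection".

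The sample size section uses a between-group difference in change of 3 μg/dL and a common SD of 11 μg/dL.

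The Discussion cites one study in which hygiene measures "were significantly associated with a reduction in indoor dust lead concentrations", and a separate review which found education ineffective on blood lead and reported that "dust control interventions may lead to little or no difference in blood lead levels". It grades the review's evidence as moderate to low quality and expects further research to change the results.

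The Abstract states a narrower aim: "The study will determine whether the intervention led to a reduction in indoor dust lead levels".

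**The concern.** The promised conclusion concerns children's lead levels, while the follow-up samples measure lead outside the body. If hand or dust lead falls, the article as worded would let that be reported as lower lead in children. Results Dissemination names participants and health policymakers as audiences, so parents could be told that their children's lead had fallen when only lead on hands and surfaces had been measured.

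The stray blood draw and the μg/dL sample size make this more than loose wording. They suggest that a blood-lead aim, sample size and conclusion sit on top of a design that follows exposure. A reader cannot tell from the article which outcome the stated 80% power belongs to.

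**Working it through.** **1. What is measured, and when**

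| Measure | Listed method | Laboratory analysis described | Repeated at three months | Measures absorbed lead |
|---|---|---|---|---|
| Hand wipe | yes | yes | yes | no |
| Floor or windowsill dust | yes | yes | yes | no |
| Yard soil | yes | yes | yes | no |
| Blood | no (one passing mention) | no | no | would do so |

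Three lead measures are repeated, and none of the three gives an internal lead value. Even if blood were drawn before the educational session, a change needs a second value, and the article describes none.

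**2. What is analysed**

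The Data analysis plan gives t-tests on lead levels without naming the sample type. The one child-level lead model that names its outcome is the mixed-effects model for hand-wipe lead. No analysis of blood lead is named.

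**3. What the sample size refers to**

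Inputs from the sample size section: difference δ = 3 μg/dL, SD σ = 11 μg/dL, power 80%, loss to follow-up 5%. The 5% significance level comes from the Data analysis plan. Its sidedness is not stated, and two-sided is assumed here.

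- Normal approximation: n = 2(z₀.₉₇₅ + z₀.₈₀)²σ²/δ² = 2 × (1.960 + 0.842)² × 121/9 ≈ 211.1, so 212 per group.
- t-based solution: 212.01, rounded up to 213 per group, which is the stated figure.
- One-sided 5% (normal approximation): 167 per group, which does not match, so the two-sided assumption fits.
- Allowance for loss: 213 × 1.05 = 223.65, so 224 per group and 2 × 224 = 448 in total, as stated.
- Power by the normal approximation: 80.4% at 213 per group and 82.3% at 224.

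The arithmetic is sound. The unit is the difficulty. μg/dL is mass per volume of fluid, and it is the unit in which the Background gives the reference level for lead. The dust standards that the article says it will apply are in µg/ft², mass per area, and soil is analysed for lead content. A difference of 3 and an SD of 11 in μg/dL cannot be carried over to wipe or soil results, so the 80% power is not established for any outcome that the study is described as following.

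**4. Whether the claim could simply mean hand-wipe lead**

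The Data analysis plan does use the term lead levels for hand wipes and for homes, so the reading is possible. Two places count against it. The Discussion uses the phrase about childhood lead immediately after reporting a review of blood lead, and the sample size is in μg/dL.

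**5. Whether exposure can stand in for absorbed lead**

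The article offers no evidence that it can. Its cited review reports that dust control may make little or no difference to blood lead. With moderate-to-low quality evidence this does not prove that dust control fails, but it does prevent the step from lower dust lead to lower lead in children from being taken for granted.

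**The case against.** The strongest defence is that the article is mostly about exposure. The Abstract limits its conclusion to indoor dust lead and ties the awareness campaign to lead exposure. The closing sentence of Possible outcomes is hedged: it speaks of a potential to protect communities from exposure. Hand-wipe lead is a genuine child-level exposure measure. No test or sample depends on the disputed sentence. The full protocol, which is not shown, may contain blood sampling at both visits.

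Much of this stands, and it rules out several stronger readings that a reader might infer:

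- That the article's own evidence shows dust lead falling while blood lead does not. It does not: the dust result and the blood result come from different sources, and no population is described in which the two parted.
- That the expected effect on blood lead is about nil. The review's finding is worded as a possibility, and the article says that the evidence may change.
- That the Abstract overreaches too. It is already confined to what the samples can show.
- That the closing sentence of Possible outcomes claims a health benefit. It claims a potential reduction in exposure.

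The defence does not rescue the sentence on childhood lead levels or its echo in the Discussion. Both are stated without that limit, and the blood draw and the μg/dL figures make the internal-lead reading the natural one. The possibility of blood sampling in the full protocol does not remove the conflict between what this article says in different sections.

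**Conclusion.** The point holds as a mismatch between the stated conclusion and the measured outcomes. As described, the study can estimate three-month change in lead on children's hands and on indoor surfaces, and in yard soil. It cannot estimate change in absorbed lead, because none of the three repeated lead measures captures it and no follow-up blood sample is described. The sample size of 213 per group reproduces, but only for a μg/dL outcome that the article does not follow.

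This rests on two assumptions: that the article lists its lead measures completely, and that μg/dL is the intended unit and not a slip for a surface or soil unit. If the unit is a slip, the power statement still needs correcting. If the full protocol takes blood at both visits, the article's methods list is what must change, and the conclusion could then be wider.

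**What to change.** 1. In Possible outcomes and the main Discussion, state the conclusion as change over three months in lead on children's hands and indoor surfaces, describe this as exposure, and say that absorbed lead is not assessed.
2. Reconcile the blood draw mentioned under Personal hygiene intervention with the four methods under Data collection procedure.
3. Reconcile the μg/dL difference and SD in the sample size section with the outcome actually followed. Either re-express the power for a measured outcome, in its own unit and with its own SD, or state that the 80% figure does not apply to the measured outcomes.
4. Leave the Abstract's conclusion as it is.

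Items 1 and 2 are wording changes and remain possible although data collection has begun. Their price is a narrower headline claim. Item 3 costs more than wording: it needs an SD for hand-wipe or dust lead, which the article does not give, or an open statement that power for those outcomes was not established.

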### Results dissemination

We aim to disseminate the results from the study to the participants, and policymakers in the health sector through conference and stakeholder presentations and official report. Furthermore, publish the findings of the study in peer-reviewed publications.

### Study progress

The study has received scientific approval and ethical clearance to commence with the research project. The study pilot stage is completed, and data collection has commenced.

## Discussion

A research study has shown that there has been significant growth in the number of households and housing developments, close to the TSFs in South Africa [15]. Furthermore, the study stated that the implications for many residences downwind mine dumps justify ongoing monitoring efforts and educational programmes [14]. Occasionally, two strategies are implemented to reduce pollution from such mine dumps i.e., spraying of mine tailings dumps with water and rehabilitation through planting grass. However, these strategies are often deemed ineffective, since grass withers during the dry season in particular, and sprayed water is rapidly absorbed or evaporated. The current extent of environmental contamination from mine dumps and potential health impacts in nearby areas has been researched, the findings showed that participants identified mine dumps as the biggest source of dust [16]. Other studies have explored the acceptability and feasibility of changing housekeeping behaviour to reduce childhood lead exposure [17]. A study by Feit et al. found that certain personal and domestic hygiene interventions were feasible and acceptable to the study community and were significantly associated with a reduction in indoor dust lead concentrations [16]. However, there is a need to conduct further trials in developing countries to determine the effectiveness of interventions for the prevention of lead [18]. A review by Nussbaumer-Streit et al. found that educational interventions were not effective in reducing blood lead levels and dust control interventions may lead to little or no difference in blood lead levels [19]. However, the quality of evidence was moderate to low, meaning that future research is likely to change these results. No further research has yet been undertaken to evaluate the impact on childhood lead levels of a community-based lead exposure reduction programme focused on personal and domestic hygiene. In particular, there remains a gap in knowledge regarding household hygiene interventions to reduce exposure to lead in communities living close to mine dumps in South Africa, particularly among children. This study, which intends to evaluate the impact of a household hygiene intervention comprised of an educational and domestic household hygiene intervention to reduce mining-related dust exposure, will address this need. The study holds the potential for a cost-effective measure to reduce exposure to mining-associated toxic substances, for hundreds of thousands of households living in the shadow of mining operations and other sites of elevated exposure to toxic substances from industrial sources.

## Data Availability

Data sharing is not applicable to this article as no data sets have been generated or analysed during the current study.

## Abbreviations

TFS: Tailing Storage Facilities
SAMRC: South African Medical Research Council
U: University of Johannesburg
NRF: National Research Council
